## Materials and methods

### Study design

This is a cross-sectional, laboratory-based observational study conducted in a single session. Outcome assessors and data analysts will be masked to group allocation and experimental condition. Physiotherapists and neuropsychologists carry out the initial assessments and conduct the interventions. Data are stored automatically, and the technologists are responsible for analysing the data obtained.

The schedule for enrolment, intervention and evaluation in the study can be found in Fig 1.

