### Participants

Participants are divided into two groups: young adults (18–39 years) and older adults (≥65 years). Inclusion criteria are: age between 18–39 years for the young group or ≥65 years for the older group; ability to understand spoken and written Spanish sufficiently to follow the study information and instructions; corrected or uncorrected vision sufficient to view the image-based tasks; ability to walk safely over short distances in the laboratory setting, with or without usual assistive devices; and willingness to provide written informed consent. Participants are included if they wish to take part voluntarily and do not present any of the following exclusion criteria: illness, injury or previous trauma that contraindicates muscle exertion, balance exercises and/or walking; physical or mental illness that contraindicates exposure to emotionally stressful stimuli, such as severe depression or psychosis; or difficulty understanding the study information and signing the consent form.

To calculate the sample size, an a priori power analysis was performed. The significance level (α) was set at 0.05, with a statistical power (1 – β) of 0.80, assuming a medium effect size (f = 0.25) to detect the main interaction effect between the group factor (younger vs. older adults), and the stimulus factor (non-stressful vs. stressful) in the context of a 2x2 Mixed ANOVA (F-test, two tails). The selection of a medium effect size is justified because the induction of emotional stress causes a robust and quantifiable functional disruption in older adults’ balance reactions, which has been demonstrated in previous studies [12]. G*Power version 3.1.9.7 was used, and it was determined that the required sample size was 27 participants per group. Assuming a potential dropout rate of 10%, the minimum initial sample size is 30 participants for each group.

Young participants are recruited from various schools at the University of Alcalá (UAH), the Complutense University of Madrid (UCM) and other settings such as sports clubs or student associations. Older participants are recruited through contacts at the University for Older Adults at UAH, the Alcalá City Council, associations, residential centres and others.

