Participants are recruited by consecutive non-probabilistic sampling and no randomization is necessary, as they will be classified into young or older adults according to age. The first participant was recruited on 27 November 2024. Participant recruitment is currently ongoing and will conclude in July 2026. The study results are expected in December 2026.

Participant information is dissociated from personal data through a coding system: each participant is assigned a code from the outset that identifies them. This unique code is recorded on a list prior to data collection, which is accessible only to the researchers involved in the project. The data collected during the assessments are securely stored under lock and key in the evaluation room. Participants are free to withdraw from the study at any time, without giving any reason and without any adverse consequences to their rights, well-being, or access to care. Concomitant treatments of participants are permitted during the study, as the measurement of variables involves no risk, harm, or discomfort, and will be conducted in a single session only.

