#### Outcome measurements.

The primary outcome measures are:

Changes in muscle activity [31], monitored through surface electromyography (EMG). EMG signals are recorded using Delsys Trigno system devices (Delsys Inc., Boston, USA), offline mode, 1259 Hz sampling bilaterally on the biceps brachii, multifidus, gluteus medius, biceps femoris, medial gastrocnemius, vastus lateralis and tibialis anterior. Electrodes are placed following SENIAM guidelines [32]. After placement and prior to the experimental session, two maximum voluntary contractions (MVCs) are performed for each muscle, with a six-second rest in between. These MVCs are used for data normalisation in subsequent analyses. Time-based EMG outcome measures include the root mean square (RMS), synchronisation of activation between muscle groups, and the ratio of activation between muscles. Frequency-based measures include the median frequency (MDF). EMG data are collected only during motor task testing, both at baseline (t_1_) and during the experimental test (t_2_) for all participants. No EMG recording occurs during baseline physical assessments (SPPB, Mini-BESTest/TUG, FRT), which characterize participant frailty prior to stress exposure (Fig 2).Ground pressure is measured using a custom-made Fitness MAT DEV KIT 1.9 mat (80 × 80 cm) developed for this project (Sensing Tex S.L., Sant Cugat del Vallès, Spain). This mat includes pressure sensors that provide precise information on weight distribution and participant behaviour during weight-shifting tasks [33]. The mat features a sensing area of 160 × 56 cm and a matrix of 2,240 sensors with a spatial resolution of 20 mm between sensors (80 × 28 matrix), local pressure mapping. Each pressure sensor has a measurement range of 20–10,000 mmHg, with 10% accuracy and a linearity coefficient of 0.99. Data are collected using a 12-bit resolution electronic unit with Bluetooth and USB connectivity. Pressure data are recorded during motor task tests at both baseline (t_1_) and the experimental test (t_2_).Acceleration and deceleration during object manipulation are measured using WT9011DCL devices (WitMotion ShenZhen Co. Ltd., ShenZhen, China). These triaxial IMUs are attached to the bottles participants must handle during fine motor task tests. Data are recorded during both baseline (t_1_) and experimental (t_2_) sessions for all participants.Balance, additionally assessed using the TUG and FRT before and after the experimental session.

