### Procedure

All study procedures are completed in a single laboratory visit. The study is conducted in the laboratories of the University of Alcalá (UAH), located in the Polytechnic Building and the Nursing and Physiotherapy Building. The researcher first provides verbal explanation of the study, answers all questions, and gives participants the information sheet (attached as Supplementary Information S1 File) to read, take home, and discuss with others as needed. Participants confirm understanding and sign the Informed Consent form only when ready. Firstly, participants read the information sheet and sign the Informed Consent form. Following this, baseline cognitive and physical assessments are carried out (Fig 2).

During the baseline test (t_1_) and the experimental test (t_2_), all participants perform the same tasks and wear both the Delsys Trigno system devices and the Hexoskin vest.

The baseline test (t_1_) is conducted first. Fixed order (low- then high-arousal) mimics real-life stress exposure patterns for ecological validity and avoids carryover effects from randomization. Participants are asked to sit on a stable chair and view low-arousal IAPS images for three minutes. After this period, a signal is given for them to begin the motor task test (gross motor, fine motor and balance tasks). This motor task test involves standing up from the chair, walking 2.3 metres over the pressure mat to a table, emptying the contents of one bottle (water) into another positioned on the table, turning around, walking back to the chair and sitting down again (Fig 3). Low-arousal IAPS images continue to be projected during the motor task test (Fig 2).

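### The protocol says outcome assessors are masked, but visible age groups and a fixed condition order rule this out for the TUG and FRT

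*Protocol article*

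**What the plan says.** Under Study design, the article makes an unqualified masking statement covering two roles and two factors: "Outcome assessors and data analysts will be masked to group allocation and experimental condition". The next two sentences divide the work. First, "Physiotherapists and neuropsychologists carry out the initial assessments and conduct the interventions". Then, "Data are stored automatically, and the technologists are responsible for analysing the data obtained".

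Under Participants, the groups are defined by age, 18–39 against 65 and over, and there is no allocation step: "no randomization is necessary, as they will be classified into young or older adults according to age". Under Procedure, one order applies to everyone: "Fixed order (low- then high-arousal) mimics real-life stress exposure patterns for ecological validity and avoids carryover effects from randomization".

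The primary outcomes are EMG, ground pressure, bottle acceleration and a fourth item: "Balance, additionally assessed using the TUG and FRT before and after the experimental session". Baseline physical assessment places the first TUG and FRT in the initial battery. Procedure places the repeat straight after the high-arousal motor task, before the EMG devices and vest come off, and does not say who carries it out.

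**The concern.** Masking of outcome assessors is a property that readers use to judge detection bias. Here it is stated as a fact about the study, yet other sections of the same article describe a design in which an in-person assessor learns both masked factors by observation.

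The planned model is a mixed ANOVA with a group factor and a time-point factor, and the sample size was set for their interaction. An assessor who sees the age group and knows the time point knows which cell of that interaction is being measured. The Introduction also gives a direction: high-arousal images are expected to produce some instability, and in older adults these effects could raise fall risk. If administration or scoring of the TUG or FRT leaves room for judgement, expectation could act in the direction being tested. A final report repeating the masking sentence would claim protection that these two tests do not have, and would place them on the same footing as device-recorded signals.

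**Working it through.** No calculation in the plan bears on this point, so the check sets the sections side by side, one masked factor at a time.

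1. **Who is an outcome assessor?** The TUG and FRT are listed under primary outcomes (Outcome measurements). Whoever administers them is therefore an outcome assessor on any ordinary reading, and Study design makes no exception for them.

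2. **Masking to group.** Group is age. The smallest possible gap between a young and an older participant is 65 − 39 = 26 years. Both tests are done with the participant present, so group membership is visible. As there is no allocation, there is no list whose concealment could help.

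3. **Masking to condition.** According to the Abstract, the first TUG and FRT precede the low-arousal condition and the second follow the high-arousal condition. With one order for all, first test means before the stressor and second test means after it, without exception. A separate assessor brought in only for the repeat could infer the same from the schedule.

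4. **Staffing.** The initial assessments, which include the first TUG and FRT, are assigned to the same professions that conduct the exposure. The article names professions and not individuals, and names nobody for the repeat. The overlap is thus documented only at baseline and by profession. Steps 2 and 3 do not depend on it.

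5. **Other outcomes.** EMG, pressure, bottle acceleration, heart rate variability and respiratory rate are recorded by devices, and the unease scale is marked by the participant. An assessor has little influence on the recorded value at acquisition.

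6. **Analysts.** Technologists analyse stored data. They need not meet participants, and group and session labels can be replaced by codes. Masking them is achievable.

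7. **Which errors would matter?** Let b with subscripts for group (Y, O) and time (1, 2) be the mean error that an assessor's knowledge adds to a TUG or FRT reading.
   - The bias in the interaction contrast is (b_O2 − b_O1) − (b_Y2 − b_Y1).
   - If knowledge of the time point shifts both groups by the same d, this is d − d = 0, and the interaction is untouched. The average time effect is shifted by (d + d)/2 = d.
   - If the shift d occurs in older adults only, the interaction is biased by d − 0 = d, and the average time effect, with equal groups, by (d + 0)/2 = d/2.

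   The document gives no value for d, so no magnitude follows. The algebra shows only that the interaction is exposed to error that differs between age groups, which requires knowing both factors. Steps 2 and 3 show that the assessor does know both.

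**The case against.** The strongest reply is that the sentence was meant for those who process the sensor data. They are a separate team, the data are stored automatically, and for them masking is realistic. An article also condenses the full protocol, and the version submitted to the ethics committee, which is not shown, may describe the procedure. On this view little is at stake, because most primary measures come from devices and an error common to both age groups drops out of the interaction.

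Part of this stands. The sensor outcomes are not compromised at acquisition, analyst masking is feasible, and only error that differs by age group reaches the interaction. But the sentence names assessors separately from analysts and makes no exception for two primary outcomes measured in person. No procedural detail held elsewhere could hide a participant's age, or the time point under a single order, from the person running the test.

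Several stronger readings are tempting and are not supported:

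- A reader might infer that exposure staff perform both TUG and FRT measurements. The article assigns them only the initial assessments and is silent on the repeat.
- A reader might infer that timing is by hand and reach is read by eye. That is plausible, but no instrument is named, so it remains an assumption.
- A reader might infer that analysts see uncoded labels. The article describes participant codes and does not say whether group and session labels are coded. That silence is not evidence that they are left open.
- A reader might conclude that the TUG and FRT should lose their primary status. An inaccurate masking statement calls for disclosure. It does not by itself justify changing declared outcomes in a study already enrolling.

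**Conclusion.** The statement is wrong as written for the TUG and FRT. Assessor masking to age group fails because age is visible, and assessor masking to condition fails because the order is fixed. Each reason is sufficient for its own factor. The scope is two tests within the primary outcomes. It does not extend to device recording, and the analyst half of the sentence can be made good.

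The conclusion rests on two assumptions: that the TUG and FRT are administered in person, as their description implies, and that the person doing so knows the study schedule. No size of bias is claimed, and none can be derived from the document. What changes is the claim that the report may make about detection bias on these tests, and it is worth correcting before analysis.

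**What to change.** Replace the masking sentence with one that separates the roles, for example:

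*Assessors administering the TUG and FRT are not masked to age group or time point. Analysts of the sensor data work with group and session labels replaced by neutral codes until pre-processing and feature extraction are fixed.*

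State who performs the TUG and FRT after exposure. In the report, keep both as primary outcomes and label them unmasked wherever their results are interpreted.

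Because the order is fixed, the relabelling should also cover file names and any clock times in the recordings, since either could reveal the session.

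The cost is a less favourable masking statement and a relabelling step before pre-processing. No change to design, sample size or outcome status is needed. The article has recruitment ending in July 2026 and results expected in December 2026, so on that timetable the correction can be made before the final analysis.

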**Fig 1 pone.0341744.g001:**
[figure not shown]
SPIRIT diagram. Schedule for enrolment, intervention, and assessment of the study. ACE-R, Addenbrooke’s Cognitive Examination-Revisado; ECog, Everyday Cognition Scale; EMG, electromyography; EVA, Visual Analogue Scale; FRT, Functional Reach Test; GDS, Geriatric Depression Scale de Yesavage; HRV, Heart Rate variability; Mini-BESTest, Mini Balance Evaluation Systems Test; MMSE, Mini Mental State Examination; RR, Respiratory Rate; SPPB, Short Physical Performance Battery; TAVEC, Test de Aprendizaje Verbal España-Complutense; TMT, Trail Making Test; TUG, Timed Up and Go Test; VFT, Verbal Fluency Test.

### Ethical approval and trial registration

The study is conducted in accordance with the recommendations of the Declaration of Helsinki and has been approved by the Ethics Committee for Research and Animal Experimentation of the University of Alcalá (CEIP/2023/5/110). A copy of the protocol submitted to the ethics committee can be found in Supplementary Information S2 File. Furthermore, the study has been registered on ClinicalTrials.gov (NCT06682754).

### Participants

Participants are divided into two groups: young adults (18–39 years) and older adults (≥65 years). Inclusion criteria are: age between 18–39 years for the young group or ≥65 years for the older group; ability to understand spoken and written Spanish sufficiently to follow the study information and instructions; corrected or uncorrected vision sufficient to view the image-based tasks; ability to walk safely over short distances in the laboratory setting, with or without usual assistive devices; and willingness to provide written informed consent. Participants are included if they wish to take part voluntarily and do not present any of the following exclusion criteria: illness, injury or previous trauma that contraindicates muscle exertion, balance exercises and/or walking; physical or mental illness that contraindicates exposure to emotionally stressful stimuli, such as severe depression or psychosis; or difficulty understanding the study information and signing the consent form.

To calculate the sample size, an a priori power analysis was performed. The significance level (α) was set at 0.05, with a statistical power (1 – β) of 0.80, assuming a medium effect size (f = 0.25) to detect the main interaction effect between the group factor (younger vs. older adults), and the stimulus factor (non-stressful vs. stressful) in the context of a 2x2 Mixed ANOVA (F-test, two tails). The selection of a medium effect size is justified because the induction of emotional stress causes a robust and quantifiable functional disruption in older adults’ balance reactions, which has been demonstrated in previous studies [12]. G*Power version 3.1.9.7 was used, and it was determined that the required sample size was 27 participants per group. Assuming a potential dropout rate of 10%, the minimum initial sample size is 30 participants for each group.

Young participants are recruited from various schools at the University of Alcalá (UAH), the Complutense University of Madrid (UCM) and other settings such as sports clubs or student associations. Older participants are recruited through contacts at the University for Older Adults at UAH, the Alcalá City Council, associations, residential centres and others.

Participants are recruited by consecutive non-probabilistic sampling and no randomization is necessary, as they will be classified into young or older adults according to age. The first participant was recruited on 27 November 2024. Participant recruitment is currently ongoing and will conclude in July 2026. The study results are expected in December 2026.

Participant information is dissociated from personal data through a coding system: each participant is assigned a code from the outset that identifies them. This unique code is recorded on a list prior to data collection, which is accessible only to the researchers involved in the project. The data collected during the assessments are securely stored under lock and key in the evaluation room. Participants are free to withdraw from the study at any time, without giving any reason and without any adverse consequences to their rights, well-being, or access to care. Concomitant treatments of participants are permitted during the study, as the measurement of variables involves no risk, harm, or discomfort, and will be conducted in a single session only.

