To assess whether the emotionally stressful stimulus produces psychophysiological effects in participants, secondary outcome variables will first be assessed: HRV, RR, and VAS of unease. Once the effect of stress has been verified, changes in the primary outcome variables will be evaluated: muscle activity (RMS y MDF), ground pressure, acceleration and deceleration, TUG, and FRT. All analyses will be conducted using mixed factorial ANOVAs, assessing the between-subjects factor GROUP (young, older adults) and the within-subjects factor TIMEPOINT (baseline, experimental). Type I error will be set at α = 5%, and partial eta squared (*η*_*p*_*²*) will be calculated as a measure of effect size. To control for multiplicity across the different outcome measures, p-values will be adjusted using the Benjamini–Hochberg procedure. Significant results will be subjected to Bonferroni-corrected post hoc *t*-tests, and Cohen’s *d* effect sizes will be calculated.

Additionally, subgroup analyses will be conducted within the older adult group, distinguishing between different levels of cognitive impairment and frailty status. The degree of cognitive impairment and frailty status will be determined based on the initial neuropsychological assessment. Correlational analyses between cognitive variables and physical test results will also be carried out.

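### GROUP is an unrandomised factor with no sex balancing stated and no sex term in the model, so unequal sex mixes could shift the GROUP x TIMEPOINT interaction if sex modifies the stress response

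*Protocol article*

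**What the plan says.** Under Participants, the protocol article defines the two groups by age alone. The young are recruited from schools of two universities and "other settings such as sports clubs or student associations". For the other group, "Older participants are recruited through contacts at the University for Older Adults at UAH, the Alcalá City Council, associations, residential centres and others". On sampling it says: "Participants are recruited by consecutive non-probabilistic sampling and no randomization is necessary". The eligibility criteria do not mention sex, and the article states no quota, matching or stratification by sex.

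Under Statistical analysis: "All analyses will be conducted using mixed factorial ANOVAs", with the "between-subjects factor GROUP (young, older adults) and the within-subjects factor TIMEPOINT (baseline, experimental" levels. Demographic variables are described but enter no model. The planned subgroup analyses are by cognitive impairment and frailty within the older group.

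The sample size in Participants targets the group-by-stimulus interaction.

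**The concern.** In a 2 x 2 mixed design the interaction is the difference between groups in mean within-person change. Using each person as their own control removes any characteristic that shifts both measurements equally. It does not remove a characteristic that alters the size of the change. If such a characteristic is more common in one group, its effect is counted in GROUP x TIMEPOINT.

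Sex is a reasonable candidate to deal with because it is not a consequence of ageing, so adjusting for it takes away nothing the study wants to measure. Fitness or SPPB score could carry part of the age effect itself.

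At stake is how the contrast the study was sized on is interpreted. A significant interaction would be read as greater vulnerability with age, when part of it could be a difference in sex composition. The Benjamini–Hochberg adjustment deals with multiplicity and does not remove such a shift.

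**Working it through.** **The plan's own figures.** Inputs from Participants: f = 0.25, α = 0.05, power 0.80, 27 per group, 10% dropout. The dropout step reproduces: 27 / (1 − 0.10) = 30. With noncentrality f² x N x 2 / (1 − ρ), the total of 54 is the N for 80% power if the correlation between repeated measures, which is not stated, is about 0.2. On the scale of SDs of change, the planned effect is 2f x √(2 / (1 − ρ)):
- ρ = 0: 0.5 x √2 = 0.71 SD
- ρ = 0.5: 0.5 x √4 = 1.0 SD

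**Shift in the interaction.** With p the share of women and δ the sex difference in stress-induced change (in within-sex SDs of change), and no true age effect:

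shift = (p_older − p_young) x δ

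**Assumed inputs.** The documents give neither p nor δ. I took δ from 0.2 to 0.8 SD and three pairs of sex shares. I then simulated 27 per group (100,000 trials per cell) and applied the two-group test on change, which is equivalent to the 2 x 2 interaction test, without sex in the model. The first rate in each cell holds the number of women fixed at the nearest whole numbers (14 v 19, 11 v 22, 8 v 22). The second lets it vary by chance around the stated shares.

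| Women, young v older | Shift, δ = 0.2 to 0.8 | δ = 0.2 | δ = 0.3 | δ = 0.5 | δ = 0.8 |
|---|---|---|---|---|---|
| 50% v 70% | 0.04 to 0.16 SD | 5.1 / 5.2% | 5.3 / 5.6% | 5.5 / 6.3% | 6.3 / 8.5% |
| 40% v 80% | 0.08 to 0.32 SD | 5.9 / 6.0% | 7.0 / 7.1% | 10.5 / 10.8% | 18.4 / 19.4% |
| 30% v 80% | 0.10 to 0.40 SD | 6.4 / 6.6% | 8.3 / 8.3% | 14.1 / 14.5% | 28.1 / 27.6% |

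**With sex in the model.** A separate simulation (20,000 trials per scenario; splits of 11 v 16, 9 v 18 and 8 v 19 of 27; δ = 0.3, 0.5, 0.8) gave a mean bias of about zero and false-positive rates of 4.7–5.2% once sex, that is SEX x TIMEPOINT, was included.

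**Chance imbalance.** If both groups are drawn from sources with half women, a gap of 20 points or more still occurs with probability 0.13 (30 per group: 0.16), and of 30 points or more with probability 0.02 (0.03).

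**Price of adjustment.** The error degrees of freedom for the interaction fall from 52 to 51. The variance of the interaction estimate is multiplied by 1 / (1 − r²), where r² = (gap / 2)² / [p̄(1 − p̄)] and p̄ is the mean share of women:
- 50 v 70: 0.01 / 0.24 = 0.042, factor 1.04
- 40 v 80: 0.04 / 0.24 = 0.167, factor 1.20
- 30 v 80: 0.0625 / 0.2475 = 0.253, factor 1.34

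Starting from 80% power (noncentrality 8.15 on 52 df) and dividing by these factors, power becomes about 78%, 72% and 67–68%. This ignores any reduction in residual variance from the sex term.

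**The case against.** A reader might infer from the recruitment lists that the sex mix does differ between the groups. The documents do not support that. Sports clubs and residential centres suggest differences in fitness and living situation, not in sex, and the lists partly overlap, since both include a university and associations. Nor do the documents give any sex difference in the response to the images. Both conditions must hold for the interaction to shift. This objection stands and limits the point to a possibility.

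The same argument could be made for any unbalanced modifier. That is true. Sex is singled out only because it is easily recorded and can be adjusted for without removing an effect of ageing.

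Modest gaps do little harm. At 20 points the false-positive rate stays near 5–8%, and material inflation needs a gap of about 40 points together with a sizeable sex difference. Even the largest shift in the table, 0.40 SD, is below the planned 0.71 to 1.0 SD. This also stands.

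It would also be too strong to say that the problem would go unseen. Categorical variables are to be tabulated, so an imbalance would probably show in the baseline description. A table shows the imbalance but does not remove its effect from the interaction.

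Finally, an article may leave covariates and quotas to a fuller document. The ethics protocol (S2 File, cited under Ethical approval and trial registration) is not shown and could add balancing. This caveat stands for recruitment. It is weaker for the model, because the article names its factors for all analyses.

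**Conclusion.** The point holds as a conditional weakness, and correcting it is a cheap improvement. The article's design neither balances sex between two unrandomised groups nor includes sex in the model, so the interaction can absorb a sex contrast if the mix is unequal and sex modifies the change. For assumed sex differences of 0.2 to 0.8 SD of change and 27 per group, the false-positive rate runs from about nominal (20-point gap) to about 18% (40 points) or 28% (50 points), the last two only at the top of the assumed range.

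It would go too far to conclude that the groups are imbalanced, that the interaction is invalid, or that the stress effects within each age group are confounded. The within-group comparison uses each person as their own control, so it is not confounded by sex in this way.

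**What to change.** Add SEX and SEX x TIMEPOINT to the mixed model for every outcome, fixed before analysis. Read GROUP x TIMEPOINT from that model and report the unadjusted result beside it. Do not add fitness or SPPB to this analysis, since they may carry part of the age effect.

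Recruitment is stated to run until July 2026. Where feasible, steer what remains towards a similar sex mix in both groups. If the ethics protocol already does so, say so in the article.

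The cost is one error degree of freedom for the interaction test and almost no precision if the sexes are balanced. Power is lost to the extent shown in the working if they are not, which is a further reason to balance while it is still possible. A late quota may slow recruitment and, with accrual to date unknown, may not fully equalise the groups.
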